# Preventing and lessening exacerbations of asthma in school-age children associated with a new term (PLEASANT): study protocol for a cluster randomised control trial

**DOI:** 10.1186/1745-6215-14-297

**Published:** 2013-09-16

**Keywords:** Asthma, Childhood asthma, Asthma exacerbation, Cluster randomised controlled trial, Primary care, Public health intervention, Unscheduled medical appointments

## Abstract

**Background:**

Within the UK, during September, there is a pronounced increase in the number of unscheduled medical contacts by school-aged children (4–16 years) with asthma. It is thought that that this might be caused by the return back to school after the summer holidays, suddenly mixing with other children again and picking up viruses which could affect their asthma. There is also a drop in the number of prescriptions administered in August. It is possible therefore that children might not be taking their medication as they should during the summer contributing to them becoming ill when they return to school.

It is hoped that a simple intervention from the GP to parents of children with asthma at the start of the summer holiday period, highlighting the importance of maintaining asthma medication can help prevent increased asthma exacerbation, and unscheduled NHS appointments, following return to school in September.

**Methods/design:**

PLEASANT is a cluster randomised trial. A total of 140 General Practices (GPs) will be recruited into the trial; 70 GPs randomised to the intervention and 70 control practices of “usual care”. An average practice is expected to have approximately 100 children (aged 4–16 with a diagnosis of asthma) hence observational data will be collected on around 14000 children over a 24-month period. The Clinical Practice Research Datalink will collect all data required for the study which includes diagnostic, prescription and referral data.

**Discussion:**

The trial will assess whether the intervention can reduce exacerbation of asthma and unscheduled medical contacts in school-aged children associated with the return to school after the summer holidays. It has the potential to benefit the health and quality of life of children with asthma while also improving the effectiveness of NHS services by reducing NHS use in one of the busiest months of the year.

An exploratory health economic analysis will gauge any cost saving associated with the intervention and subsequent impacts on quality of life. If results for the intervention are positive it is hoped that this could be adopted as part of routine care management of childhood asthma in general practice.

**Trial registration:**

Current controlled trials: ISRCTN03000938 (assigned 19/10/12) http://www.controlled-trials.com/ISRCTN03000938/.

UKCRN ID: 13572

## Background

Asthma exacerbations and deaths are known to be seasonal [1]. A number of reports have shown peaks in asthma exacerbation in school aged children with asthma associated with the return to school following the summer vacation [2-10]. These studies mainly report hospital admissions, although one study has reported peaks both in hospital admissions and all medical contacts [10].

Children returning to school are exposed to a variety of novel respiratory challenges including allergens and viruses, at a time of changing climactic conditions. It has previously been shown that viral infection and allergen exposure in allergen sensitised asthmatics are associated with increased hospital admissions for acute asthma [11]. The same study demonstrated the protective effect of inhaled corticosteroids on acute asthma exacerbations in a paediatric asthma population [11].

In previous research by the study team a random sample of around 75,000 school age (5–16 years) children were observed, using a data set from selected general practices within the General Practice Research Database (now the Clinical Practice Research Datalink [12]), who had a documented medical diagnosis of asthma. Age (within 2 years) and sex matched controls from the same practice were also taken [13]. The investigation confirmed the increase in unscheduled medical contacts in children with asthma throughout the year with an approximate doubling in medical contacts compared to non-asthmatic children. Regression analysis showed that children with asthma were approximately twice as likely as controls to have unscheduled medical contact and were more likely to see their doctor around the return to school. If asthmatic children were at a constant increased risk of medical contacts throughout the year Figure 1 would show a random scatter of the residuals in England. However, around the return to school there was a pronounced positive increase in the value of residuals (a similar pattern was observed for Scotland). This indicates that at this time there was a greater than expected increase in the number of contacts by children with asthma compared to controls.

**Figure 1 F1:**
[figure not shown]
**Mean residuals for excess medical contacts for children with asthma for over controls in England.** The vertical lines represent, from left to right, the 1st September, 1st January and 1st April with LOESS smoothing curve that enables trends to be seen [13].

It could therefore be argued that July and August are a good time to have asthma; the pollen season is almost over, school age children are not at school and so have less opportunity to pick up any viral infections that are going through the population.

In the same study we also observed a drop in prescriptions for inhaled steroids in August immediately preceding the return back to school with 25% fewer prescriptions in August compared to July and September [13] (see Figure 2). This drop in prescriptions precedes the viral challenge of a return back to school. We further showed that patients who received a prescription for inhaled corticosteroid had 0.14 fewer contacts per patient (95% CI 0.12 to 0.16, P < 0.001, England; 95% CI 0.10 to 0.18, P < 0.001, Scotland) than those who did not receive an August prescription.

**Figure 2 F2:**
[figure not shown]
Average daily prescriptions by month for England and Scotland.

To interpret the figure of 0.14: hypothetically imagine a cohort of 200 children with asthma on inhaled corticosteroids, where 100 receive an August prescription and 100 do not. If the 100 patients with a prescription make a total of 50 unscheduled medical visits (0.5 mean visits/patient) then 64 unscheduled medical contacts would be made by those not receiving a prescription (0.64 mean visits/patient; difference 0.14). Hence, per 100 children with asthma on inhaled corticosteroid not receiving a prescription in August there is an excess of 14 unscheduled medical contacts. Unplanned medical contacts cost the NHS: £36 for a contact in surgery; £121 for a GP home visit [14]; £59 to £142 for an emergency department contact if not admitted and £74 to £249 if admitted; £385 for a non-elective short stay for asthma without complications [15].

It is therefore likely that children who stop taking or reduce their inhaled corticosteroids over the summer months or run low of other medications, and fail to restart them before the return to school, are more at risk of acute asthma exacerbation.

The PLEASANT trial will be observing the effect of a brief postal intervention sent to school aged children (4–16) with asthma. A letter, will be sent by their General Practitioner (GP) at the start of the school summer holidays, encouraging continuation with their prescribed asthma medication before the start of the new school year. We will assess the impact this has on subsequent unscheduled NHS contacts and reduction in exacerbation of asthma.

## Methods/Design

### Study design

PLEASANT is a cluster randomised trial. A total of 140 General Practices (GPs) will be recruited into the trial; 70 GPs randomised to the intervention and 70 control practices of “usual care” (Figure 3). An average practice is expected to have approximately 100 children eligible hence data will be collected on over 14000 children over a 12 month period. This is a non-commercial, portfolio study adopted by the Primary Care Research Network.

**Figure 3 F3:**
[figure not shown]
Trial summary.

### Primary research objective

The aim of the trial is to assess if a brief postal intervention reduces the number of unscheduled medical contacts after the return to school. The primary objective of the study is to assess whether the intervention reduces the September peak in total medical contacts and subsequent exacerbations in asthma.

### Primary outcome measure

1. The proportion of patients aged between 5–16 who have an unscheduled medical contact in September

### Secondary outcome measures

1. The proportion of patients who have an unscheduled medical contact in the period September-December

2. The total number of medical contacts (scheduled and unscheduled) per patient in September and in the period September-December

3. The time to first unscheduled medical contact in September and in the period September-December

4. The proportion of patients who have a medical contact (either scheduled or unscheduled) in September and in the period September-December

5. The total number of medical contacts (either scheduled and unscheduled) per patient in September and in the period September-December

6. The time to first medical contact in September and in the period September-December

7. The proportion of patients who have an unscheduled medical contact in September and in the period September-December associated with a respiratory diagnosis

8. The number of unscheduled medical contacts per patient in September and in the period September-December associated with a respiratory diagnosis

9. The time to first unscheduled medical contact associated with a respiratory diagnosis in September and in the period September-December

10.  The number of prescriptions per patient in the month of August

11.  The number of prescriptions in the 12 months following the intervention

12.  The proportion of patients who have a scheduled medical contact (for example asthma review) in August

13.  The proportion of patients who have a scheduled medical contact (for example asthma review) in the 12 months following the intervention.

The above analyses will be undertaken on patients aged 5 years - 16 years, since asthma is difficult to diagnose in children below this age [16,17]; patients aged < 5 will be analysed separately to these (see the statistical analysis section for more details).

### Setting and site recruitment

The trial will be conducted within primary care with GPs that are currently part of Clinical Practice Research Datalink (CPRD). Invitation letters will be sent out, via CPRD, to all current active GP CPRD sites within England and Wales. 140 sites are expected to be recruited within 6-month (1st January 2013 to 30th June 2013) based on CPRD’s previous experience of recruiting GPs to research trials [12].

Support will also be accessed from the Primary Care Research Network (PCRN) to advertise the trial. Interested practices will be forwarded further information regarding the practicalities of delivering on the study including sign up to CPRD, if they are not already members, as this is a requirement for participation.

### Randomisation

The randomisation will be stratified by size of practice to ensure that there is an equal sample size – in terms of number of school age asthmatic children – in each arm of the trial. The allocation ratio will be 1:1. The randomisation list will be generated using the Stata statistical software. Randomisation will be done centrally: upon confirming their participation, practices will be randomised to one of the two arms; intervention vs usual care. Randomisation will be undertaken by a statistician within the University of Sheffield’s Clinical Trials Research Unit (CTRU), in line with the randomisation plan.

GPs randomised to intervention will be asked to send the postal intervention to eligible patients; GPs randomised to control will continue with usual care and will not be required to do anything further.

### Site compliance

A member of the study team will be responsible for site set up and maintaining on-going contact with the GP setting. Site set up will be done either via telephone or video conferencing. For those sites that prefer a face-to-face contact the study team will either do the visit (if within a reasonable distance) or liaise with the appropriate local PCRN to do the visit on their behalf.

An electronic GP study information pack will be sent out to all sites with a flow chart to show progress through the trial period, timing of intervention, information required from sites and subsequent NHS service support cost payments.

### Withdrawal

Practices are free to withdraw from the trial at any time. This will be documented on a site withdrawal form. Any data already collected during the course of the trial up to the point of withdrawal will be used in the final analysis. With permission from the site data will be retained from the practice as supplied by CPRD.

### Target population for intervention

The population targeted for the intervention will be school aged asthmatic children (aged between 4 and 16 years) registered with a GP.

### Inclusion criteria

Children aged between 4 and 16 years of age as of 1st September 2013 with a coded diagnosis of asthma who have been prescribed asthma medication in the previous 12 months.

### Trial intervention

A brief postal intervention (letter) has been designed specifically for the PLEASANT trial, developed with input from the study team, which includes a GP, Psychologist and Consultant Respiratory Paediatrician as well as the trial steering committee. It has also been discussed in detail, and reviewed, at two patient and public events that included school aged children with asthma and their parents.

The letter highlights the potential risks associated with stopping, or running low on, asthma medication during the school summer holidays and the effect this may have on exacerbation of asthma when returning to school. It encourages maintaining, or restarting if stopped, medication and to contact the GP or practice nurse if a prescription is required or clarification is needed on the dose. A copy of the intervention/letter is available upon request and will be published on the PLEASANT website from October 2013.

The intervention will be sent, from the GP, to the parents/carers of children with asthma at the beginning of the summer school holidays (week commencing 29th July 2013).

### Data collection

#### Clinical Practice Research Datalink

The CPRD is a computerised database of anonymised longitudinal medical records from primary care [18]. The CPRD are able to capture all medical contacts, from prescription request through to out of hours contacts, along with the reason for the contact. This therefore negates the need to request this information from the GP, reduces practice burden, and ensures complete data sets.

CPRD will extract data from GP medical records 3 times; baseline (NHS contacts for the previous 12 months) and at 1 month and 12 months post intervention. The study team will not have access to any patient identifiable data and will receive all data fully anonymised.

### Allocation of scheduled versus unscheduled contacts

Every NHS service contact is coded by the GP practice and captured within the practice database. Using these codes we will allocate to either scheduled or unscheduled contact.

A scheduled contact is defined as any contact that is part of the planned care for the patient, for example an asthma review; a medical review; repeat prescription or immunisation. An unscheduled contact will be any contact not part of the patient’s care plan that is either patient initiated or as a result of illness.

To ensure the allocation of scheduled and unscheduled contacts are robust an adjudication panel, consisting of 3 GPs, will independently review the prescription and diagnosis codes allocating to either scheduled or unscheduled contact.

### Statistics

#### Sample size

From previous research in the CPRD practice population 30% of school age asthmatic children had at least one unscheduled medical contact within the month of September [13]. We postulate that the intervention may reduce the number of children who have unscheduled medical contacts from 30% to 25% (i.e. an absolute reduction of 5%). This gives an effect size of 5%. The average practice size in the CPRD is 8,294. We thus anticipate circa 100 school-age asthmatic patients per practice (based on 12% of a practice being school age children and 11% of school-age children having asthma). Hence, to detect a difference of 5% with 90% power and two-sided significance level of 5%, with an intra-class correlation (ICC) of 0.03 to account for clustering we require 70 practices per arm. The sample size of 140 practices would equate to approximately 14,000 school age asthmatic patients.

Ukoumunne et al. [19] give estimates of ICCs for patients with respiratory symptoms in symptoms in General Practice. Based on the work of Ukoumunne et al. an ICC of 0.03 is a conservative estimate. The power of the study for ICCs of 0.01, 0.02, 0.03, 0.04 and 0.05 is respectively 99.4, 96.0, 90.0, 83.1 and 76.2%.

As a further sensitivity analysis we will investigate the effect of practices not sending out the letter as planned. Suppose 10 practices failed to send out the letter, these would still be included in the primary analysis under the intent-to-treat principle. However, the effect that could be observed would be reduced to 4.3%. Under the sample assumptions (ICC = 0.03, etc.) the power for the same sample size is reduced to 79.3%. This is a little under 80% but it does demonstrate that the study is reasonably robust to at least one deviation in the planned design.

#### Data analysis

The study periods are defined in three stages. The primary study period is 1st – 30th September 2013, since this is the period when the intervention is felt likely to impact. The extended study period is 1st September - 31st December 2013, since asthma-related appointments are more frequent in the entire period. The follow-up period is 12 calendar months from 1st September 2013 to 31st August 2014.

The primary analyses will be by intent-to-treat among patients aged 5–16 years as of 1st September 2012. The primary endpoint (the proportion of patients who have an unscheduled medical contact in September) will be analysed by logistic regression in which the covariates will include the individual's age; gender; number of contacts the previous September; the trial arm (intervention or control); and the design/cluster effect of general practice as a random effect.

The same approach will be used for analyses based on the extended period. The proportion of patients who have an unscheduled medical contact, the proportion of patients who have any medical contact; and the proportion of patients who have an unscheduled medical contact associated with respiratory illness. The number of unscheduled medical appointments per patient in the extended period; the total number of medical contacts (scheduled and unscheduled) per patient in the extended period; the number of unscheduled medical contacts per patient associated with a respiratory diagnosis in the extended period; the number of prescriptions per patient in the month of August; and the number of prescriptions per patient in the 12 months following the intervention will be analysed in an analogous approach to the primary endpoint. A random effects negative binomial model will be fitted, including the same covariates as above. Further analyses will address the time to first medical contact (defined as the number of days from the start of school term (2nd September 2013) to the date of first appointment, up to and including December 2013, the time to first medical contact up to and including December 2013, and the time to first unscheduled medical contact associated with a respiratory diagnosis. These analyses will be conducted using a random effects ("shared frailty") regression model including the same covariates as described previously.

Patients aged 4–5 will be analysed separately to those aged 5–16, since the diagnosis of asthma is more controversial in this age group; it is often not practical to measure variable airway obstruction below the age of 5 making diagnosis of asthma difficult [16,17]. The impact of the intervention in patients under 5 will be compared to that seen in the main analysis to assess whether the intervention appears to benefit younger children. Additional exploratory analyses will investigate whether the impact of the intervention is related to age or other characteristics of the patient.

A detailed description of the statistical analysis of efficacy and safety outcomes will be written in the trial Statistical Analysis Plan which will be finalised prior to receiving post-intervention data from CPRD. The trial will be reported using the principles highlighted in the CONSORT statement for reporting cluster RCTs [20].

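### Randomisation is stratified by practice size, but the stated analysis models omit it; if size predicts contacts, the tests are slightly conservative (minor)

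*Protocol article*

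**What the plan says.** On allocation, the Randomisation section of the protocol article states: "The randomisation will be stratified by size of practice to ensure that there is an equal sample size" (counted as school-age children with asthma in each arm). It adds: "The allocation ratio will be 1:1". Size of practice is the only stratification factor named.

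On analysis, the Data analysis section specifies "logistic regression in which the covariates will include" age, then "gender; number of contacts the previous September; the trial arm (intervention or control); and the design/cluster effect of general practice as a random effect". For the count outcomes it says: "A random effects negative binomial model will be fitted, including the same covariates as above". The time-to-first-contact analyses use a shared frailty model, again with the same covariates. No section of the article puts practice size into any model.

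The same section defers the detail: "A detailed description of the statistical analysis of efficacy and safety outcomes will be written in the trial Statistical Analysis Plan". That plan is to be final before post-intervention data are received. It is not available here.

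**The concern.** Stratifying by size balances the arms on size, so any variation in contact rates that follows size is largely removed from the comparison of arms. A model without size does not know this. It leaves the size-related variation in the practice random effect, treats it as chance variation between arms, and reports a standard error that is too large. The random effect therefore does not replace the stratification factor; it is where the unexplained size variation ends up. None of the named covariates is a practice-level measure of size.

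Between-practice variation also dominates the precision of this trial, as the working shows, so even a modest explained share of it is visible in the standard error. At stake are intervals somewhat wider than the design warrants, a test run below its nominal 5%, and a small amount of power left unused, across the primary and the model-based secondary analyses.

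**Working it through.** **Inputs from the Sample size section:** 30% v 25%; two-sided 5%; ICC 0.03; 70 practices per arm; about 100 children per practice; stated power 90.0% (99.4, 96.0, 90.0, 83.1 and 76.2% for ICC 0.01 to 0.05).

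**Input not in the documents (assumption):** R, the share of between-practice variance explained by practice size. I show 0 to 30%, with 5 to 20% as the working range.

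**Step 1: reproduce the plan's power.** Design effect = 1 + 99 × ICC, which is 3.97 at ICC 0.03. Variance factor = 0.30 × 0.70 + 0.25 × 0.75 = 0.3975. SE of the difference = √(0.3975 × 3.97 / 7000) = 0.01501. Power = Φ(0.05/0.01501 − 1.96) = 91.5%. For ICC 0.01 to 0.05 this gives 99.7, 97.0, 91.5, 84.6 and 77.6%, each within 1.5 points of the stated figure. The plan's power thus reproduces closely with no credit taken for stratification.

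**Step 2: how much of the variance lies between practices.** 3.97 = 0.97 (within) + 100 × 0.03 (between), so the between-practice share is 3.00/3.97 = 76%.

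**Step 3: effect of leaving size out.** With size balanced by stratification, the true design effect is 0.97 + 3.00 × (1 − R). The model without size still works with 3.97. Then:
- SE ratio r = √(true design effect / 3.97)
- actual type I error without size = 2 × [1 − Φ(1.96/r)]
- power without size = Φ[(0.05 − 1.96 × 0.01501) / SE_true]
- power with size = Φ(0.05/SE_true − 1.96)

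Example, R = 20%: true design effect 3.37; SE_true = √(0.3975 × 3.37 / 7000) = 0.01383; r = 0.921; type I error = 2 × [1 − Φ(2.127)] = 3.3%; power without size = Φ(1.487) = 93.2%; power with size = Φ(1.654) = 95.1%.

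| R (assumed) | True design effect | SE ratio | Type I error without size | Power without size | Power with size | Points forgone |
|---|---|---|---|---|---|---|
| 0% | 3.97 | 1.000 | 5.0% | 91.5% | 91.5% | 0 |
| 5% | 3.82 | 0.981 | 4.6% | 91.9% | 92.4% | 0.6 |
| 10% | 3.67 | 0.961 | 4.2% | 92.3% | 93.4% | 1.1 |
| 20% | 3.37 | 0.921 | 3.3% | 93.2% | 95.1% | 1.9 |
| 30% | 3.07 | 0.879 | 2.6% | 94.0% | 96.6% | 2.6 |

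Differences were taken before rounding. These are normal approximations on the proportion scale with perfectly balanced strata, so they show the order of size and are not exact for the random-effects logistic model.

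**The case against.** The strongest objection is that the covariate list is open. It says what the covariates will include, not that they are all, and the detail goes to a statistical analysis plan that is not shown and may already contain the stratum. This stands in part: nothing in the article excludes practice size, so the point is not an error that invalidates the analysis. But the article does name the model terms and carries them into every secondary model, so someone fitting the model as written would leave out the one variable on which the allocation was constrained.

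Second, size may not be prognostic. The stated reason for stratifying is equal numbers of children per arm, not a link with contact rates. This stands, and it makes the consequence conditional.

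Third, the model already adjusts for each child's contacts in the previous September, which may absorb some of any size-related difference. This also stands. What counts is what size explains beyond prior contacts, so the relevant R could lie at the low end of the range or below it.

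A reader might infer more than the documents support:
- **That the trial risks a false positive finding.** It does not; the error makes the test conservative.
- **That the trial falls short of its planned 90% power.** It does not; that figure takes no credit for stratification.
- **That adding size raises power from 91.5% to as much as 95.1%.** The 91.5% applies only when size explains nothing. Where size does explain something, stratified allocation already helps the model without it, so the fair comparison is between the two power columns on the same row.

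**Conclusion.** The stated primary and secondary models omit the stratification factor, and the random effect does not make up for it. The consequence is small, conservative and conditional on practice size predicting contacts beyond the covariates already listed. If size explains 5 to 20% of between-practice variance, correct intervals are about 2 to 8% narrower, actual type I error without the term is about 4.6 to 3.3%, and about 0.6 to 1.9 points of power are forgone against the adjusted model. This assumes 100 children per practice, ICC 0.03 and balanced strata. If size explains none of it, there is no loss. The share is my assumption; the documents give no figure for it. Severity: minor.

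**What to change.** Before post-intervention data arrive, prespecify the practice-size stratum used at randomisation (or practice size as a continuous term) as a fixed effect in the primary logistic model and in the secondary negative binomial and shared frailty models, or state why it is left out. If the statistical analysis plan already does this, the only action is to confirm that the two documents agree.

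The cost is one model term and at most a few degrees of freedom among 140 practices. No new data are needed, because practice size has to be known to randomise. Settling it in advance also removes a later choice between size-adjusted and unadjusted results.

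### The primary model uses each child's own previous-September contacts but not the practice's previous-September rate, so precision available from data already being extracted is probably lost

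*Protocol article*

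**What the plan says.** The primary outcome is "The proportion of patients aged between 5–16 who have an unscheduled medical contact in September" (Primary outcome measure). The Data analysis section specifies a logistic regression whose terms, beyond the age and gender of the child, are given as "number of contacts the previous September; the trial arm (intervention or control); and the design/cluster effect of general practice as a random effect". These covariates are also carried into the count and time-to-event models. No practice-level baseline rate is listed. The Randomisation section stratifies by practice size only, so the design does not balance practices on their earlier outcome rate either.

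The data for such a rate are collected anyway: the first CPRD extraction is "baseline (NHS contacts for the previous 12 months"), for all practices. The Sample size section works "to detect a difference of 5% with 90% power and two-sided significance level of 5"%, and "with an intra-class correlation (ICC) of 0.03 to account for clustering we require 70 practices per arm". It takes no credit for any covariate. The detailed analysis is left to a statistical analysis plan, to be finalised before post-intervention data are received.

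**The concern.** When practices are randomised and each contributes about 100 children, the standard error of the arm effect comes largely from differences between practices. A covariate helps most if it explains those differences. The practice's own September 2012 proportion is the primary outcome measured at baseline at the level of randomisation, so it is the natural candidate.

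The planned covariate is the child's own number of contacts. With this many children per practice, a random-intercept model estimates its coefficient almost entirely from comparisons within practices. That one slope is then also applied to differences between practice means. If practice rates persist from year to year more strongly than one child's contacts do, the slope is too small for the between-practice relation, and both the residual practice variance and chance imbalance in practice baselines are only partly removed. The covariate as worded also counts contacts of any kind, while the outcome counts unscheduled contacts.

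The confidence interval may then be wider than the collected data allow. This would matter most in the protocol's own weaker scenarios: 79.3% power if ten practices fail to send the letter, and 76.2% at ICC 0.05.

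**Working it through.** **Inputs from the Sample size section.** The control rate is 30% ("30% of school age asthmatic children had at least one unscheduled medical contact within the month of September"), the effect is "from 30% to 25% (i.e. an absolute reduction of 5"%), there are 70 practices per arm, the ICC is 0.03, and the two-sided level is 5%. On cluster size: "We thus anticipate circa 100 school-age asthmatic patients per practice".

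**Reproducing the stated power.** Let m be the cluster size and DE = 1 + (m − 1) × ICC. Then SE² = DE × (0.30×0.70 + 0.25×0.75) / (70m), and power = Φ(effect/SE − 1.96).

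- With m = 100, power for ICC 0.01 to 0.05 is about 99.7, 97.0, 91.4, 84.5 and 77.6%, within 2 points of the stated figures.
- With m = 82 it is 99.4, 96.0, 90.0, 83.1 and 76.2%, exactly as stated. For ICC 0.03: DE = 1 + 81×0.03 = 3.43; SE² = 3.43×0.3975/5,740; SE = 0.0154; 0.05/0.0154 − 1.96 = 1.28; power 90.0%.
- With ten non-sending practices the effect is 5% × 60/70 = 4.29%, which gives 79.1% against the stated 79.3%.

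I use m = 82 below because it matches the protocol's own series. Results with m = 100 are close.

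**Between-practice share of the variance of a practice proportion,** m × ICC / DE:

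- ICC 0.03: 3.00/3.97 = 76% (m = 100) or 2.46/3.43 = 72% (m = 82).
- m = 100: 50% at ICC 0.01 and 84% at ICC 0.05.

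**Effect of adjustment.** Two quantities are assumed because the documents do not give them: s, the within-practice correlation of a child's outcome in the two Septembers (0.1-0.2), and c, the year-to-year correlation of true practice rates (0.3-0.9). The correlation of observed practice proportions across years is

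r = (m × ICC × c + (1 − ICC) × s) / DE.

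Relative to no adjustment, the variance of the arm effect is multiplied by 1 + s² − 2sr with the child-level covariate only, and by 1 − r² with the practice rate added. The difference is (r − s)². It cannot be negative, and it vanishes when the practice-level and child-level correlations coincide.

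Worked case, s = 0.1 and c = 0.7 at ICC 0.03: r = (1.722 + 0.097)/3.43 = 0.53. The factors are 0.90 and 0.72, so power is 92.7% and 96.9%. The ratio 0.72/0.90 = 0.80 is equivalent to about 20% fewer practices.

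Power (%), planned model → practice rate added, first for s = 0.1, then for s = 0.2:

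| c | ICC 0.03, 5% effect | ICC 0.03, ten non-senders | ICC 0.05, 5% effect |
|---|---|---|---|
| 0.3 | 91.1→91.7; 92.0→92.1 | 80.6→81.4; 81.8→82.0 | 78.0→79.1; 79.3→79.6 |
| 0.5 | 91.9→94.0; 93.5→94.6 | 81.8→85.1; 84.2→86.1 | 79.4→84.0; 82.1→84.7 |
| 0.7 | 92.7→96.9; 94.8→97.4 | 82.9→90.4; 86.5→91.6 | 80.8→91.0; 84.9→91.9 |
| 0.9 | 93.4→99.2; 96.1→99.5 | 84.1→96.3; 88.8→97.3 | 82.2→98.1; 87.8→98.7 |

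**Simulation check.** This used 140 practices of 100 children, 300 runs per scenario, ICC about 0.03, s about 0.09-0.20, and a linear random-intercept model on the binary outcome. The child-level covariate left 60-95% of the between-practice variance. Adding the practice rate left 89-91% at c = 0.3, 76-79% at 0.5, 43-48% at 0.8 and 29-34% at 0.9.

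**The case against.** The strongest reply is that nothing here is in error. The planned model respects the clustering and already adjusts for history. Its type I error and interval are valid, and randomising 140 practices deals with chance imbalance. The 90% power was claimed without any adjustment, and the planned covariates can only be expected to improve on it. All of that stands. A reader might infer that the primary analysis is biased, or that the trial is underpowered; the documents support neither.

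A reader might also infer that power is certainly lost, or that the child-level covariate does almost nothing. That goes too far. The size of the gain depends wholly on correlations the documents do not give. It is near zero if practice rates are unstable from year to year, and it shrinks if the child-level correlation is higher: at s = 0.3 and ICC 0.03 it is 0.0, 0.5, 1.4 and 1.7 points for c = 0.3, 0.5, 0.7 and 0.9. In the simulations the child-level covariate removed 5-40% of the between-practice variance. The protocol regards ICC 0.03 as conservative; at ICC 0.02 and c of 0.5-0.9 the gain is only 0.4-2.0 points, and at ICC 0.01 at most about 0.2.

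Finally, the covariate list is worded so that terms could be added, and the analysis plan is not shown. This leaves room for the fix but does not remove the point: the article does choose how history enters, and it chooses the child level only.

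**Conclusion.** The point holds as a matter of efficiency. With history entered only at child level, part, and often most, of the between-practice variance can remain unexplained, and precision is probably lost. For s of 0.1-0.2, the gain from adding the practice rate, in power points at c = 0.3, 0.5, 0.7 and 0.9, is:

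- ICC 0.03: about 0-0.6, 1-2, 3-4 and 3-6.
- Ten non-sending practices: about 0-1, 2-3, 5-8 and 9-12.
- ICC 0.05: about 0-1, 3-5, 7-10 and 11-16.

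These figures rest on the assumed correlations, equal practice sizes, a linear approximation to the logistic model, and a child-level covariate that measures the same outcome as the endpoint. Baseline proportions from small practices are noisier, and that effect was not examined. Within the formulas the practice rate never lowers power, apart from the one degree of freedom, which they ignore.

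**What to change.** Before post-intervention data arrive, in the Data analysis section or the analysis plan:

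- Keep the planned covariates and the random practice effect.
- Word the child-level covariate as the child's unscheduled contacts in September 2012.
- Prespecify one added practice-level covariate in the primary model: the proportion of the practice's eligible children aged 5-16 with an unscheduled contact in September 2012, from the baseline CPRD extract.
- In the secondary contact models, use the matching practice-level baseline where that extract covers the same period.

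The cost is one derived variable, one practice-level degree of freedom out of about 138, and a slight change in the conditional odds ratio, as with any covariate added to a logistic model. No new data are needed. Timing matters: the same addition made after outcomes are seen would look data-driven.
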